### 2.6. Sample Size

The estimated sample size was determined for the primary outcome variable (HRQoL-pain) using the EHP-30 questionnaire and calculations from a previous study to detect a mean difference between control and intervention groups of 24.7 (28.4 ± 18.7 vs. 3.66 ± 18.4; Gonçalves, Barros and Bahamondes [40]). Assuming an α error of 0.05, a power of 85% and an effect size of 1.34 (based on the results of the reference study), we need a sample of 10 participants for each group. Assuming a possible 30% dropout rate, we will recruit a minimum of 13 participants per group (*n* = 26). G*Power v. 3.1 (Düsseldorf University, Düsseldorf, Germany) was used to calculate the sample size.

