## Abstract

Aim: The ‘Physio-EndEA’ study aims to explore the potential benefits of a therapeutic exercise program (focused on lumbopelvic stabilization and tolerance to exertion) on the health-related quality of life (HRQoL) of symptomatic endometriosis women. Design: The present study will use a parallel-group randomized controlled trial design. Methods: A total of 22 symptomatic endometriosis women will be randomized 1:1 to the Physio-EndEA or usual care groups. The ‘Physio-EndEA’ program will consist of a one-week lumbopelvic stabilization learning phase followed by an eight-week phase of stretching, aerobic and resistance exercises focused on the lumbopelvic area that will be sequentially instructed and supervised by a trained physiotherapist (with volume and intensity progression) and adapted daily to the potential of each participant. The primary outcome measure is HRQoL. The secondary outcome measures included clinician-reported outcomes (pressure pain thresholds, muscle thickness and strength, flexibility, body balance and cardiorespiratory fitness) and patient-reported outcomes (pain intensity, physical fitness, chronic fatigue, sexual function, gastrointestinal function and sleep quality). Discussion: Findings of this study will help to identify cost-effective non-pharmacological options (such as this exercise-based intervention) that may contribute to the improvement of HRQoL in symptomatic endometriosis women.

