## 2. Materials and Methods

### 2.1. Study Design and Setting

Encompassed in a multidisciplinary research project (EndEA, Endometriosis y Exposición Ambiental), the ‘Physio-EndEA’ study is a parallel-group randomized non-inferiority trial (ClinicalTrials.gov, NCT03979183) based on a 1 + 8-week exercise program that will be conducted in 26 patients diagnosed with endometriosis (*n* = 13 experimental group vs. *n* = 13 control group) in Granada (Spain). The organizational and participants flow is presented in Figure 1. Primary and secondary outcomes will be assessed at baseline and immediately after intervention. Moreover, we will also evaluate the long-term impact of this exercise program by a final assessment 1 year after intervention with similar characteristics to the post-program evaluation. Physio-EndEA will be carried out at CUIDATE unit (http://csaludable.ugr.es/pages/dossierultimo/%21, accessed on 15 June 2021), a research unit for rehabilitation in oncology and related diseases. The protocol has followed the recommendations of the Standard Protocol Items: Recommendations for Intervention Trials (SPIRIT) checklist [51,52], and Figure 1 shows the SPIRIT diagram. This study was approved by the Clinical Research Ethics Committee of Granada, Government of Andalusia, Spain (code: 0792-N-18). ‘Physio-EndEA’ study was registered with ClinicalTrials.gov (code: NCT03979183).

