### 2.9. Data Analysis

Since this study aims to determine the potential benefits of therapeutic exercise on the HRQoL of endometriosis patients, statistical analyses will be performed on an intention-to-treat basis. Only those participants that would have attended at least 75% of the sessions and completed at least two assessments (baseline and one evaluation of the two follow-ups) will be included in the analyses. The worst-case value will be used to replace missing data, after a previous reported procedure.

Mean and standard deviation will be used to describe variable scores at baseline and both follow-up measurements (postprogram and 1 year). Additionally, the Shapiro–Wilk test will be used to assess the normality of the distribution of the variables. To evaluate the ability of the randomization process to avoid differences between groups at baseline, Student’s t-test and chi-square test will be used to compare continuous and categorical data, respectively. An equivalent statistical approach will be conducted in case of non-parametrical data (Mann–Whitney and Kruskal–Wallis tests).

To evaluate the influence of treatment on outcome scores, a repeated-measure ANCOVA between the three time points (baseline, postprogram and 24 weeks later) will be used to examine the between-group and within-subject differences. Patient age, years since diagnosis, education level, marital status and the presence of heavy bleeding during the menstruation period will be used as covariates. To complete the analysis, we will report effect size (Cohen d) and level significance attending to interaction effects (group x time) to examine intergroup effects and to determine whether these were negligible (d < 0.2), small (0.2 < d > 0.5), moderate (0.5 < d > 0.8) or large (d > 0.8).

The statistical significance will be set at α = 0.05. Statistical analyses will be conducted on the Statistical Program for Social Sciences (IBM, SPSS 24.0).

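### Adding 30% to 10 per group does not cover a 30% dropout: 13 per group leaves about 9, below the protocol's own requirement, and the abstract gives 22 women instead of 26

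*Protocol article*

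**What the plan says.** Section 2.6 (Sample Size) takes its inputs from an earlier trial of yoga: a between-group difference of 24.7 points on the EHP-30 pain domain, with standard deviations of 18.7 and 18.4. It then sets the design values: "Assuming an α error of 0.05, a power of 85% and an effect size of 1.34". From these it derives 10 women per group and adds an allowance for loss: "Assuming a possible 30% dropout rate, we will recruit a minimum of 13 participants per group", 26 in total. G*Power is named as the software, but the test family and the number of sides are not given. Section 2.9 (Data Analysis) adds only this: "The statistical significance will be set at α = 0.05".

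The total is stated in several places. Section 2.1 says the study "will be conducted in 26 patients diagnosed with endometriosis", 13 in each group, and section 2.3.2 repeats 13 for the control group. The abstract says otherwise: "A total of 22 symptomatic endometriosis women will be randomized 1:1".

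Loss reduces the analysed sample. Section 2.3.1 counts a woman as a dropout if she attends fewer than 12 of the 16 sessions. Section 2.9 analyses only women with at least 75% attendance and a baseline plus at least one follow-up assessment.

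**The concern.** The dropout allowance is meant to ensure that the required number of women remains once the expected share is lost. Here it does not: 30% off the recruited 13 gives fewer than the 10 that the same paragraph requires. The power claim is the only justification given for the trial's size, and at this size one woman per group moves power by about 4 to 5 percentage points. With two enrolment totals in print, a reader also cannot tell which number marks complete recruitment. Finally, because the test is not named, the 85% cannot be checked uniquely, and the reasonable candidates give different answers.

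**Working it through.** **Inputs.** All come from section 2.6 unless noted: α = 0.05; target power 85%; d = 1.34; 10 evaluable per group; 30% dropout; 13 recruited per group. Allocation is 1:1 (section 2.7). Sidedness is not stated, so both are shown.

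**Effect size.** Pooled SD = √((18.7² + 18.4²)/2) = √344.125 = 18.55. Then d = (28.4 − 3.66)/18.55 = 24.74/18.55 = 1.334, so the stated 1.34 is slightly generous but acceptable.

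**Reproducing 10 per group.** With a two-sided normal approximation, n = 2(1.960 + 1.036)²/1.34² = 10.0004 per group. Power at 10 is Φ(1.34·√(10/2) − 1.960) = Φ(1.036) = 85.0%. The stated figure is therefore reproduced, although strict rounding up would give 11.

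**Dropout allowance.**
- Used: 10 × (1 + 0.30) = 13.
- Remaining after 30% loss: 13 × 0.70 = 9.1, so about 9 per group.
- Loss that 13 can absorb while keeping 10: 1 − 10/13 = 23%.
- Number that keeps 10 after 30% loss: 10/(1 − 0.30) = 14.3, rounded up to 15 per group (30 in total).

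None of these four lines depends on the test.

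**Power by test at d = 1.34.** The t columns use the noncentral t distribution with 2n − 2 degrees of freedom and noncentrality 1.34·√(n/2).

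| n per group | two-sided normal | two-sided t | one-sided t |
|---|---|---|---|
| 9 | 81.1% | 76.1% | 85.9% |
| 10 | 85.0% | 80.9% | 89.2% |
| 11 | 88.2% | 84.8% | 91.8% |
| 12 | 90.7% | 88.0% | 93.8% |

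The smallest n reaching 85% is 12 for the two-sided t-test and 9 for the one-sided t-test. With d = 1.334 in place of 1.34, 10 per group gives 84.7% (two-sided normal) and 80.5% (two-sided t).

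**Enrolment total.** Sections 2.1 and 2.6 give 26, and sections 2.1, 2.3.2 and 2.6 give 13 per group. The abstract gives 22, or 11 per group under 1:1 allocation. No reading makes the two agree.

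**The case against.** A reader might infer that 10 per group simply fails to give 85%, and that the trial's power is 81%, or 76% after dropout. The documents do not support that as a statement of fact. Those figures belong to a two-sided t-test. That is a plausible choice given G*Power, but section 2.6 does not name it. A two-sided normal approximation returns 10 at 85.0%. A one-sided Wilcoxon-Mann-Whitney calculation (relative efficiency 0.955) also has 10 as its smallest sufficient number, with 84.3% at 9 and 87.8% at 10. So the 10 is not shown to be an arithmetic error.

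A one-sided t-test goes further: 9 per group gives 85.9%, so the target would survive 30% loss. The label "parallel-group randomized non-inferiority trial" in section 2.1 might seem to point that way. But under that test the requirement would have been 9, not 10, so it does not explain the protocol's figure. For the normal approximation and the Wilcoxon calculation, which do lead to about 10, 9 per group falls below 85%.

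Three further points are fair:
- The planned analysis is a repeated-measures ANCOVA over three time points, so no two-sample calculation need equal the trial's actual power. That is a reason to recompute the figure; it does not justify the 85%. Since the ANCOVA estimates its error variance, a known-variance approximation is also hard to defend at 10 per group.
- Thirteen is stated as a minimum, so more could be recruited. But section 2.6 itself gives 26 as the total, and sections 2.1 and 2.3.2 treat 13 per group as the size.
- Section 2.9 replaces missing values, so a woman who misses one follow-up stays in. Women who meet the section 2.3.1 definition of dropout are still left out.

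One might also read the abstract's 22 as the real target and conclude that power is far lower. At 11 per group, 30% loss leaves 7 to 8, or 63% to 70% with a two-sided t-test. Three sections of the body contradict that reading, so 22 is best taken as an inconsistency in the abstract.

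**Conclusion.** Two parts stand without any assumption about the test. The dropout inflation is wrong: 13 per group less 30% leaves about 9 where the protocol requires 10, and 13 covers 23% loss, not 30%. The abstract's 22 contradicts the 26 in the body.

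The third part is conditional. Because test and sidedness are not stated, power for 10 completers per group lies between 80.9% and 89.2% across the two-sided t, two-sided normal and one-sided t calculations. For 9 completers it lies between 76.1% and 85.9%. If a two-sided t-test was intended, 10 per group is about 4 percentage points short and 9 per group about 9 points short of 85%. All these figures rest on d = 1.34, equal groups and a simple two-group comparison rather than the planned ANCOVA.

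**What to change.** - **Abstract:** change 22 to 26 (13 per group), in line with sections 2.1, 2.3.2 and 2.6.
- **Section 2.6, test:** state the test and the number of sides used for the calculation.
- **Section 2.6, dropout:** say that 13 per group leaves 10 completers if 23% are lost, and about 9 if 30% are lost.
- **Section 2.6, power:** replace the 85% claim with the power for the named test at those numbers. If a two-sided t-test was intended, that is about 81% with 10 and about 76% with 9 completers per group. Alternatively, recompute the figure for the repeated-measures ANCOVA and state the correlation assumed between time points.

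The cost is a text correction and, on most readings, a less favourable stated power. No extra enrolment is required for it. Should the sponsor prefer to keep 10 completers per group under a 30% loss, the arithmetic consequence is 15 per group (30 in total).

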### 2.7. Randomization and Blinding

Once the baseline evaluation will be completed, participants will be included in either the therapeutic exercise intervention or the control group (1:1). For that, a computer-generated sample randomization sequence will be created by a researcher not involved in the clinical part of this study (Epidat 3.4, Xunta de Galicia, Spain). Once known, the primary investigator will communicate the assigned group to each participant. Therefore, although practitioners and participants will not be blinded, other researchers (assessors, statisticians and data managers) will be blind to group allocation. Participants will be asked not to mention any details of their treatment or their group allocation to the assessor(s) (responsible for evaluation sessions). If blinding is compromised, another assessor will be contacted and will complete the data collection.

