The second part of the intervention will lasts 8 weeks with group sessions twice per week focused on health-related fitness and motor control improvement. Each session will be divided into three sections: (1) an initial period with warm-up exercises (10 min); (2) a main period with aerobic (20–40 min) (continuous brisk walks), stretching (10–15 min) and lumbopelvic stabilization exercises (30–35 min) (taking into consideration the instructions previously learnt about motor control); and a final cool-down period of breathing and relaxation exercises. Details of the specific lumbopelvic stabilization exercises that these participants will perform are summarized in Table 1’s footnotes. Increases in both duration and intensity for aerobic exercises will be carried out based on fatigue perception. Alternatively, duration, intensity and number of repetitions for resistance exercises will be sequentially increased over time based on the adequate motor control of the lumbopelvic area, as well as fatigue perception. For that, by using the Borg Fatigue Scale [56], the physiotherapist (aided by two technicians) will daily inform about the maximum level of perceived fatigue that each patient must assume (from <11 at initial week to 13–14 at the end of the program), and thus, the women will increase or decrease the exercise intensity accordingly. For that purpose, women will be previously instructed with this scale to appropriately report their current perceived fatigue.

Adherence is defined based on the patient’s attendance to the sessions, considering as dropouts when they do not participate in at least 12 (75%) of 16 scheduled sessions. To maximize adherence, some strategies will be implemented, including adapted timetables to patient needs, music in all sessions and telephone calls following missed sessions.

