#### 2.3.2. Usual Care/Control Group

Participants randomly assigned to the control group (*n* = 13) will receive the usual treatment, which is stipulated by their gynaecologist. Additionally, during the initial evaluation session, the trained physiotherapist assessor will offer general advice about the positive effects of physical activity and a healthy lifestyle for their HRQoL. For ethical reasons, control participants will be given the opportunity to participate in an exercise program with the same characteristics of this therapeutic exercise intervention after completion of this study, although their results will not be included in the analyses.

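### The stated blinding of statisticians and data managers is not secured, because the analysis set is selected by session attendance, which only the exercise arm has

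*Protocol article*

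**What the plan says.** Section 2.7 separates two groups of people. It says that "although practitioners and participants will not be blinded", while "other researchers (assessors, statisticians and data managers) will be blind to group allocation".

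Section 2.9 declares that "statistical analyses will be performed on an intention-to-treat basis" and then restricts the set: "Only those participants that would have attended at least 75% of the sessions and completed at least two assessments" are analysed. The two assessments are baseline and at least one of the two follow-ups. The attendance condition is written for participants in general and names no arm.

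Section 2.3.1 shows which sessions are meant. It describes the exercise group and defines dropouts by attendance, "considering as dropouts when they do not participate in at least 12 (75%) of 16 scheduled sessions".

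Section 2.3.2 gives the control arm no sessions during the trial. Controls "will receive the usual treatment, which is stipulated by their gynaecologist", plus general advice at the initial evaluation. They may join an exercise program only "after completion of this study, although their results will not be included in the analyses".

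**The concern.** The two rules pull against each other. One says that the people who manage and analyse the data do not know the arms. The other selects the analysed women on a variable that exists in one arm only. Read literally, no control can meet the attendance condition, so whoever applies it has to know who is a control in order to exempt her.

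The primary outcome, the EHP-30, is self-reported by women who know their allocation. Blinding of the analyst is therefore one of the protections that remain. Section 2.9 leaves some judgement to the analyst: worst-case replacement of missing values follows a procedure that is not described there, and the parametric or non-parametric route depends on how the data look. If the arms can be recognised at that stage, the trial may report a protection that it did not have.

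**Working it through.** **Inputs**
- 13 women per arm, 26 in total (sections 2.1 and 2.6).
- Attendance cut-off: 12 of 16 sessions (section 2.3.1). Check: 12/16 = 0.75, so the 75% in section 2.9 is the same rule.
- Section 2.6 plans with "Assuming a possible 30% dropout rate". It applies this to both groups: 10 × 1.3 = 13 per group.
- The article gives no rate of attendance failure. The rates below are assumptions.

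**Route 1: the attendance data are seen.** A woman with an attendance record is in the exercise arm, and a woman without one is a control. All 26 allocations are revealed. No probability is involved.

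**Route 2: only coded arms (A/B) and an include/exclude flag are seen, and the excluded women's records stay visible.** There are two reasons for exclusion.
- Too few assessments: possible in either arm, and visible in the outcome data.
- Low attendance: possible in the exercise arm only.

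A woman flagged out although she has baseline and a follow-up can have failed only on attendance, so her code is the exercise arm. One such woman identifies both codes.

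Let p be the chance that an exercise participant attends fewer than 12 sessions, independently of the others. Then P(at least one low attender among 13) = 1 − (1 − p)^13:

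| Assumed p | Calculation | Chance of at least one |
|---|---|---|
| 5% | 1 − 0.95^13 | 49% |
| 10% | 1 − 0.90^13 | 75% |
| 20% | 1 − 0.80^13 | 95% |
| 30% | 1 − 0.70^13 | 99% |

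At p = 30% the expected number of low attenders is 0.3 × 13 = 3.9.

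**What these figures measure.** They give the chance that a low attender exists. Unmasking by route 2 also needs her to have a follow-up assessment, and the analyst to see that record with its arm code. For each p the figure is therefore an upper bound. If, as an illustration, half of the 30% (15%) were low attenders with outcome data visible to the analyst, the chance would be 1 − 0.85^13 = 88%.

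**Route 3: only eligible records are passed on.** The analyst then sees unequal numbers at most. Controls can also be lost, through missing follow-up, so the smaller code hints at the exercise arm but does not prove it.

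**The case against.** A reader might infer that the statistician must apply the attendance rule and that the stated blinding therefore cannot hold. The article does not support this. Section 2.9 is in the passive voice and gives the rule to nobody. The practitioners who run the sessions are unblinded, and section 2.8 gives each participant a coded ID, although for confidentiality. Session staff could apply the rule and forward only eligible coded records, which is route 3. This objection stands, and it is why the point is put as blinding not secured.

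A reader might also take the 99% as the chance that the arm is identified. It is not. It counts low attenders, and women who stop attending may also miss assessments. Nor can the 30% be purely a rate of attendance failure, because section 2.6 applies it to controls too. This also stands, and the figures are used only as bounds.

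The harm should not be overstated. Section 2.9 does name worst-case replacement, the normality test, the non-parametric alternatives, the repeated-measures ANCOVA, its covariates and alpha. The room for judgement is limited, though not nil.

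Finally, file handling is detail that an article may leave to the full protocol or analysis plan, and its absence alone would be no finding. What remains does not depend on that absence: two rules stated in the article conflict unless something further is arranged. Route 3 would also ask the data managers, who are declared blind, not to see which records were removed.

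**Conclusion.** The point holds as a conflict between two stated rules. The attendance condition in section 2.9 applies to one arm only, so the blinding of statisticians and data managers in section 2.7 is not secured by the plan as written.

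The size depends on what the data team sees:
- with the attendance data, all 26 allocations are revealed;
- with coded arms and visible exclusions, the chance of unmasking is at most 49% to 99% for assumed failure rates of 5% to 30%;
- with only eligible records forwarded, there is a hint from unequal numbers and no identification.

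This rests on attendance being recorded only for exercise participants, on independence between women, and on failure rates that the article does not give. It does not show that the blinding will fail. The matter should be settled before analysis, because the remedy is cheap and also removes an exclusion that falls on one arm only.

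**What to change.** Change sections 2.7 and 2.9 as follows:
1. Run and lock the primary analysis on all randomised women with outcome data, in the arm to which they were allocated, with arms coded A/B and no selection by attendance. This also fits the intention-to-treat basis that section 2.9 declares.
2. Until that lock, the session staff, who are already unblinded, hold the attendance file.
3. Merge attendance afterwards for a supportive analysis labelled as unblinded.
4. If attendance must define the primary set, remove statisticians and data managers from the blinding statement.

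The cost is wording and an order of file release, with no extra patients or visits. The downside is that the attendance-based analysis comes later and is unblinded. Moving attendance to a supportive analysis without withholding the file would not secure the blinding.
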